# Protocol for a cluster randomised control trial evaluating the efficacy and safety of treatment for latent tuberculosis infection in recent migrants within primary care: the CATAPuLT trial

**DOI:** 10.1186/s12889-019-7983-7

**Published:** 2019-11-29

**Keywords:** Tuberculosis, Public health, Respiratory medicine, Primary care

## Abstract

**Background:**

The identification and treatment of LTBI is a key component of the WHO’s strategy to eliminate TB. Recent migrants from high TB-incidence countries are recognised to be at risk TB reactivation, and many high-income countries have focused on LTBI screening and treatment programmes for this group. However, migrants are the group least likely to complete the LTBI cascade-of-care. This pragmatic cluster-randomised, parallel group, superiority trial investigates whether a model of care based entirely within a community setting (primary care) will improve treatment completion compared with treatment in specialist TB services (secondary care).

**Methods:**

The CATAPuLT trial (Completion and Acceptability of Treatment Across Primary Care and the community for Latent Tuberculosis) randomised 34 general practices in London, England, to evaluate the efficacy and safety of treatment for LBTI in recent migrants within primary care. GP practices were randomised to either provide management for LTBI entirely within primary care (GPs and community pharmacists) or to refer patients to secondary care. The target recruitment number for individuals is 576. The primary outcome is treatment completion (defined as taking at least 90% of antibiotic doses). The secondary outcomes assess adherence, acceptance of treatment, the incidence of adverse effects including drug-induced liver injury, the rates of active TB, patient satisfaction and cost-effectiveness of LTBI treatment. This protocol adheres to the SPIRIT Checklist.

**Discussion:**

The CATAPuLT trial seeks to provide implementation research evidence for a patient-centred intervention to improve treatment completion for LTBI amongst recent migrants to the UK.

**Trial registration:**

NCT03069807, March 2017, registered retrospectively.

## Background

TB remains the leading cause of death among infectious diseases globally [1]. The WHO strategy to eliminate TB prioritises screening and treatment of those at high risk of latent tuberculosis infection (LTBI) [2]. It is estimated that approximately a quarter of the world’s population (1.7 billion people) have LTBI [3]. Epidemiological modelling indicates that without successful treatment of LTBI in addition to active case finding it will be impossible to eliminate TB by 2050 [4] .

Recent migrants from high TB-incidence countries are recognized to be a group with a high LTBI prevalence and risk of TB reactivation [5]. In many high-income countries, where a high proportion of TB cases occur amongst the foreign-born, TB strategies have focused on LTBI screening and treatment programmes for this group, including England, which in 2015 made the systematic screening and treatment of LTBI in migrants a core component of its national TB control strategy [6]. However, traditional models of care are associated with low rates of completion in the LTBI cascade-of-care, with recent migrants recording the lowest rates of any at-risk group [7]. Recognising the weaknesses of traditional models of care, the End TB Strategy makes “integrated, patient-centred care and prevention” a pillar of its action-frame work for elimination and calls for urgent “research to optimise implementation” of novel strategies [2].

The London borough of Newham has been a pilot site for the national LTBI screening programme for recent migrants since 2014. Newham has the highest incidence of active TB in the United Kingdom (UK), with 86% of cases in 2014 occurring in those born outside the UK [8]. The programme in Newham has adopted a novel model of care for treating LTBI that occurs entirely within the community: GPs offer screening with an IGRA. Patients with positive results are assessed and if diagnosed with LTBI offered treatment that is monitored by a trained community pharmacist in collaboration with the patient’s GP. This is the first time in the UK that LTBI has been managed systematically outside of a specialist TB service. The proposed national model for LTBI screening in England is to screen for LTBI in primary care but for those identified with LTBI to be referred for assessment and treatment to secondary care (specialist TB services) [9]. Specialist TB services for Newham are provided by the TB clinic at Newham University Hospital, Barts Health NHS Trust.

We will conduct a pragmatic cluster-randomised, parallel group, superiority trial to evaluate the efficacy and safety of treatment for LTBI in recent migrants within primary care as compared to treatment in secondary care. The primary objective will be treatment completion (defined as taking at least 90% of antibiotic doses on pill count). The secondary objectives of the trial will assess adherence, acceptance of treatment, the incidence of adverse effects including drug-induced liver injury (DILI), the rates of active TB, patient satisfaction and the cost-effectiveness of treatment.

## Methods and design

### Study design

This is a pragmatic cluster-randomised, parallel group, superiority trial of at least 20 randomisation units (20 of 60 GP Practices) in the London borough of Newham, UK.

The cluster-randomised design was chosen because the delivery of LTBI management in primary care provided by multiple health care professionals across various locations occurs at the level of the cluster. The use of individual randomisation was not feasible because it would disrupt the delivery of a complex intervention at participating GP practices. This protocol follows the SPIRIT guidelines [10].

### Setting/intervention

The trial compares two models of care for LTBI treatment: management in the community by a GP and community pharmacist (intervention) or in secondary care by a TB doctor and TB nurse (control). The setting will be the London borough of Newham.

Since 2014, all GP practices (*n* = 60) in Newham have been contracted to screen and treat recent migrants for LTBI as a pilot site for the national LTBI screening and treatment programme. Eligible patients are those aged 16–35 years, from a country with a TB incidence > 150 per 1,000,000 per year or sub-Saharan Africa, who have arrived in the UK within the last 5 years. The CATAPuLT study protocol mirrors the existing service specification for the Newham LTBI programme. Nationally the model for LTBI care in recent migrants is to screen in primary care and to refer those with positive results to secondary care for assessment and treatment.

In the CATAPuLT trial, all GP practices will continue to screen eligible patients for LTBI. Practices will be randomised to either provide assessment and treatment for LTBI in primary care (the intervention arm) or to refer patients to secondary care (the control arm, which represents the current standard of care). The test for LTBI is an interferon gamma release assay (IGRA).

To confirm a diagnosis of LTBI, any patient with a positive IGRA must be reviewed by a doctor to exclude active TB. The medical assessment includes a history, physical examination, a chest radiograph and blood tests (full blood count, liver function tests, urea and electrolytes, c-reactive protein and blood-borne virus serology (Human Immunodeficiency Virus (HIV), Hepatitis B Virus (HBV) and Hepatitis C Virus (HCV)). Those diagnosed with LTBI are offered treatment with 3 months of Rifinah®, combination rifampicin and isoniazid therapy (Sanofi, UK), and pyridoxine.

In the intervention arm, the GP excludes active TB, and offers treatment for LTBI. The patient is asked to select one accredited community pharmacy for treatment. The borough has 16 community pharmacies that have been trained and accredited to provide LTBI treatment. Treatment is initiated and monitored by a community pharmacist. At their initial visit, the community pharmacist will counsel the patient about LTBI treatment. The patient is then issued with a 1 month supply of medication and asked to attend for liver function tests (LFTs) after 2–4 weeks. The patient attends the pharmacy at the end of each of the 3 months of treatment to assess adherence and adverse effects. In the control arm, the TB clinician and TB nurse mirror the role of the GP and community pharmacist respectively. Prior to starting treatment, a questionnaire will be used to assess knowledge about LTBI.

Follow up is identical in trial both arms: at the end of each month of treatment adherence is assessed using a pill count (or self-report if the patient fails to attend with their tablets), and the Medication Adherence Report Scale (MARS-5), a set of 5 statements about common patterns of adherence rated on a 5-point Likert scale (1 = always, 2 = often, 3 = sometimes, 4 = rarely, and 5 = never) [11]. At the first and second visits, urine is tested for metabolites of isoniazid (Isoscreen®, GFC Diagnostics, Oxfordshire, UK). At the second visit, the patient completes a satisfaction questionnaire. Prior to starting treatment, a questionnaire will be used to assess knowledge about LTBI. See Table 1.

**Table 1 Tab1:** Timetable of assessments in the CATAPuLT Trial. For Urine testing a minimum of two urine tests should be performed during the 3 months of treatment. These should be done at the review visit for months 1 and 2 of treatment, although the second may be done at the final visit instead if the patient was unable to provide a sample at either of the earlier visits, or additionally at the final visit if there are concerns about adherence, *LFTs Liver function test, **INH Isoniazid

Assessment Tool	Day 0	Day 15	Day 30	Day 60	Day 90
Questionnaire (Understanding and knowledge of LTBI)	X				
Blood tests for LFTs*		X			
Pill count / MARS5 tool			X	X	X
Questionnaire (adherence/ adverse effects)			X	X	X
Urine test (Colour and INH **metabolites)			X	X	
Patient satisfaction questionnaire				X	

### Inclusion criteria

Patients identified with LTBI aged 16–35 and who have entered the UK within the last 5 years, from a country with a WHO-estimated annual TB incidence of ≥150 per 100,000 per year or sub-Saharan Africa. LTBI is defined as a positive IGRA test without symptoms, physical signs or radiological evidence of active TB.

Between October 2017 and April 2018, Newham CCG piloted extended eligibility criteria to include those who had been resident in the UK for up to 10 years. The trial protocol was amended to mirror this change.

### Exclusion criteria

Pregnant or breastfeeding women.Patients requiring medications that cannot be safely taken with RifinahHIV infectionIndividuals with known liver disease, or abnormal liver function tests (LFTs).Diagnosis of cirrhosisChronic or active HBV or HCV infection.Previous treatment for TB or LTBIIndividuals who are unable to consent or who would usually be offered LTBI treatment under DOTEvidence of active TB (based on history, examination, blood tests and/or chest radiograph).

These exclusion criteria match the service specification for the existing local LTBI programme. IGRA positive patients with complex co-morbidities or health needs are referred to specialist TB services for assessment and treatment.

### Outcomes

#### Primary outcome –treatment completion

Completion of at least 90% of prescribed therapy as assessed by pill count. Where a patient fails to bring their medication, information will be obtained by patient report. Treatment completion will be assessed at the final patient review, approximately 3 months after treatment is commenced. To avoid bias, an independent researcher, blinded to allocation, will verify treatment completion where there is uncertainty. This outcome is defined for IGRA positive patients who accept treatment.

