#### Secondary outcomes

Proportion of participants completing < 80, 80–89.9, ≥90% of antibiotic dosages based on pill count.Treatment adherence assessed using the five-point adherence questionnaire (MARS5 tool), prescription collection and a point-of-care urine testing for metabolites of Isoniazid (Isoscreen) at monthly intervals.Treatment acceptance assessed by calculating the proportion of eligible patients that accept therapy; this is defined as those initiating treatment and attending TB clinics and community pharmacies on at least one occasion.The number of patients on treatment having adverse events including DILI leading to discontinuation of treatment or hospitalisation. Safety of treatment will be assessed every month by the pharmacist in primary care and by the TB nurse in secondary care.The incidence of active TB occurring within 2 years after enrolment. TB incidence in the intervention and control group will be compared and there will be a sub-group analysis to evaluate the effect of the intervention in those who did or did not complete treatment. This will be performed through matching the study population with the national Enhanced TB Surveillance System, where information on all reported TB cases nationally are recorded.Assessment of patient satisfaction.Evaluation of cost-effectiveness of LTBI treatment in primary care compared to secondary care.

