### Blinding

Data collection and analysis will be unblinded due to the nature of the intervention, cluster level randomisation and different data collection systems for the two study arms.

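### Patient-reported completions count the same as pill-counted ones in the primary outcome, and the blinded check has no fixed trigger that covers them

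*Protocol article*

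**What the plan says.** The Background section summarises the primary objective as treatment completion, "defined as taking at least 90% of antibiotic doses on pill count". The primary outcome section gives the fuller rule: "Completion of at least 90% of prescribed therapy as assessed by pill count", followed by the fallback "Where a patient fails to bring their medication, information will be obtained by patient report". The same fallback applies at each monthly visit in both arms (Setting/intervention): "adherence is assessed using a pill count (or self-report if the patient fails to attend with their tablets".

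On who records the outcome, the Blinding section states "Data collection and analysis will be unblinded due to the nature of the intervention" and adds as a further reason "different data collection systems for the two study arms". Data collection and management has the patients' usual care team enter the data.

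The safeguard stands in the primary outcome section: to avoid bias, "an independent researcher, blinded to allocation, will verify treatment completion where there is uncertainty".

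The Missing data section brings prescription collection into the primary outcome. Patients who withdraw without collecting every prescription are failures. Those who collected everything but missed the last visit are multiply imputed, with a sensitivity analysis that counts them as failures. The secondary outcomes include pill-count categories, MARS-5, and "prescription collection and a point-of-care urine testing for metabolites of Isoniazid (Isoscreen").

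**The concern.** A pill count and a patient's statement are different measurements, and the statement can be expected to err towards completion. The outcome rule gives them equal standing. A pharmacist reviews the tablets in one arm and a TB nurse in the other, the staff know the arm, and the data systems differ. The share of outcomes that rest on report alone may therefore differ between arms, although the article gives no figure for either arm.

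If the shares differ, over-reporting does not cancel. It enters the odds ratio as an apparent effect of the care setting, in favour of whichever arm relies more on report. The direction cannot be known in advance.

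The blinded researcher is the obvious protection, but the trigger is undefined. A patient who attends without tablets and states that all were taken may look quite certain to the person recording the visit. Such a case could pass without verification, and nothing in the article says otherwise.

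**Working it through.** **Treatment of two similar patients, from the article**

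| Patient | Status in the primary outcome | Stated sensitivity analysis |
|---|---|---|
| Collected all prescriptions, missed the final visit | Missing, multiply imputed | Yes: counted as failed |
| Attended the final visit without tablets, reports at least 90% taken | Observed completion | None stated in the article |

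The plan is cautious about the first patient. It takes the second at face value unless the case happens to be judged uncertain.

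**Inputs from Sample size:** completion 70% v 85%, a planned effect of 15 points; 442 outcomes, 221 per arm, so 442/34 = 13 per practice; ICC 0.05; coefficient of variation 0.5. The stated 268 for an individually randomised trial reproduces as 134 per arm with a continuity-corrected two-proportion formula. The present point does not depend on it.

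**Assumptions, not in the documents:** the report-only share in each arm, and the overstatement (reported minus true completion among report-only patients), taken as equal in both arms.

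**Formula:** spurious difference = (report-only share in one arm − share in the other) × overstatement.

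| Shares | Overstatement | Spurious difference | Fraction of 15 points |
|---|---|---|---|
| 30% v 10% | 15 points | 0.20 × 15 = 3.0 | 20% |
| 30% v 10% | 30 points | 0.20 × 30 = 6.0 | 40% |
| 40% v 10% | 30 points | 0.30 × 30 = 9.0 | 60% |

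**How extreme are these?** If report-only patients complete at their arm's average rate, overstatement cannot exceed 100 − 70 = 30 points at 70% true completion, or 100 − 85 = 15 points at 85%. At 70%, a 15-point overstatement means that half of the report-only non-completers are recorded as completers; 30 points means all of them. The 6- and 9-point rows are therefore ceilings.

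**Effect on the false-positive rate.** Design effect = 1 + (13 × 1.25 − 1) × 0.05 = 1.7625, where 1.25 = 1 + 0.5². Effective size = 221/1.7625 = 125.4 per arm. Take true completion of 70% in both arms, with the larger report-only share in the intervention arm. The 3-point case records 70 + 0.10 × 15 = 71.5% and 70 + 0.30 × 15 = 74.5%. With a pooled standard error of √(2 × 0.73 × 0.27/125.4) = 0.0561 and an unpooled one of 0.0560, z = (0.03 − 1.96 × 0.0561)/0.0560 = −1.43. The chance of a significant result favouring the intervention is about 8%, against a nominal 2.5%. A 6-point gap (70% v 76%) gives about 19% by the same formula.

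**The case against.** The strongest reply is that this is a condensed article without its SAP. The working definition of uncertainty, and an analysis by source of outcome, could well stand there. That is right, and a reader who infers that no planned analysis addresses report-only completions goes further than the article allows. What remains is the rule the article itself states: verification with an open trigger.

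Three other inferences are tempting and not supported:

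- *The unblinded staff choose which cases are verified.* The article does not say who decides, only that verification follows uncertainty.
- *Prescription collection serves secondary outcomes only.* The Missing data section uses it to classify withdrawals in the primary outcome and to define who is imputed. The protection is partial, because collecting tablets is not the same as taking 90% of them.
- *The objective contradicts the outcome.* The Background is a summary; the outcome and follow-up sections state the fallback openly and consistently, with follow-up described as identical in both arms.

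The secondary adherence measures are a fair partial cross-check: completion that differed by arm while urine results and collection did not would be visible. They do not settle the matter. The article does not say whether the secondary pill-count categories also accept self-report. MARS-5 is itself self-report and is described as unvalidated in LTBI. The scheduled urine tests fall at days 30 and 60, so month 3 is not routinely covered.

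**Conclusion.** The point holds as a safeguard whose trigger is badly fixed, not as proof of bias or of a missing analysis. Report-only completions enter the primary outcome on equal terms, recording is unblinded in arm-specific systems, and the article does not ensure that the blinded check reaches these cases. Its one stated sensitivity analysis of the primary outcome concerns another group.

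A reasonable illustrative size is 3 points, one fifth of the planned effect, which would raise the one-directional false-positive rate from 2.5% to about 8%. This rests on assumed shares of 30% and 10% and a common 15-point overstatement. With equal shares and equal overstatement the spurious difference is zero. Values of 6 to 9 points should not be quoted as likely. The change is worth making because it is cheap, but confidence in the size is limited.

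**What to change.** 1. In the primary outcome section, replace the uncertainty condition with a fixed trigger: the existing blinded researcher verifies every report-only completion. The extracts should have arm and data system removed and should show the prescription-collection and urine results already gathered.
2. Report the share of report-only outcomes by arm.
3. Extend the sensitivity analysis in the Missing data section so that report-only completions also count as not complete, labelled as a conservative bound on completion and not as an alternative estimate. It penalises the arm with more such cases: at 70% true completion and no over-reporting, shares of 30% and 10% would by themselves produce (0.30 − 0.10) × 70 = 14 points. It must be read with item 2.
4. Do not make two positive urine tests a hard requirement. The article gives Isoscreen sensitivity only as greater than 90%, so up to 1 − 0.9² = 19% of adherent report-only patients could fail it (assuming independent tests), before missed samples are counted.

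The cost is a source flag for each outcome, some extra cases for a researcher already in the plan, and one more model run. The article does not say whether the templates record the source. Publication is dated 29 November 2019 and data collection runs to December 2019, so the flag may have to be reconstructed from records.

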#### Secondary outcomes

Proportion of participants completing < 80, 80–89.9, ≥90% of antibiotic dosages based on pill count.Treatment adherence assessed using the five-point adherence questionnaire (MARS5 tool), prescription collection and a point-of-care urine testing for metabolites of Isoniazid (Isoscreen) at monthly intervals.Treatment acceptance assessed by calculating the proportion of eligible patients that accept therapy; this is defined as those initiating treatment and attending TB clinics and community pharmacies on at least one occasion.The number of patients on treatment having adverse events including DILI leading to discontinuation of treatment or hospitalisation. Safety of treatment will be assessed every month by the pharmacist in primary care and by the TB nurse in secondary care.The incidence of active TB occurring within 2 years after enrolment. TB incidence in the intervention and control group will be compared and there will be a sub-group analysis to evaluate the effect of the intervention in those who did or did not complete treatment. This will be performed through matching the study population with the national Enhanced TB Surveillance System, where information on all reported TB cases nationally are recorded.Assessment of patient satisfaction.Evaluation of cost-effectiveness of LTBI treatment in primary care compared to secondary care.

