### Harms

The intervention in this trial is the setting of care. There are no specific anticipated harms associated with allocation within the trial. However, patients in both arms of the trial will be treated for LTBI with a 3-month course of daily Rifinah®. This preparation is licenced for use in the UK and is currently recommended for LTBI [20, 22].

Trial participants will be monitored for adverse events (AEs) and serious adverse events (SAEs) at each monthly review and are asked to undertake a blood test to assess liver function after 2 to 4 weeks of treatment.

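### The listed safety outcome names DILI only when it leads to stopping treatment or hospitalisation, while the stated objective is DILI incidence; because stopping depends partly on the randomised care team, the count mixes harm with monitoring

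*Protocol article*

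**What the plan says.** The abstract (Methods) and the last paragraph of the Background both list among the secondary aims "the incidence of adverse effects including drug-induced liver injury". Neither limits this to events with a particular consequence.

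Under Secondary outcomes the measure becomes "The number of patients on treatment having adverse events including DILI leading to discontinuation of treatment or hospitalisation". The next sentence adds: "Safety of treatment will be assessed every month by the pharmacist in primary care and by the TB nurse in secondary care".

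One liver test is scheduled during treatment. Table 1 places it at Day 15. Under Setting/intervention the patient is "asked to attend for liver function tests (LFTs) after 2–4 weeks", and under Harms participants "are asked to undertake a blood test to assess liver function after 2 to 4 weeks of treatment". The planned schedule is common to both arms: "Follow up is identical in trial both arms".

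The Blinding section states: "Data collection and analysis will be unblinded due to the nature of the intervention, cluster level randomisation and different data collection systems for the two" arms. Blinded verification by an independent researcher is described for treatment completion (Primary outcome). The article does not mention it for DILI.

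**The concern.** The randomised intervention is the setting of care. In one arm a GP and a community pharmacist assess the patient, order the liver test and respond to it. In the other arm a TB clinician and a TB nurse do so. When DILI enters the outcome because treatment was stopped, the count reflects two things: how often liver injury occurred, and how often the team found it and stopped treatment. The second is a property of the service being compared.

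The two can pull in opposite directions. A patient who did not attend for the test, or whose abnormal result led to no change, is counted as event-free unless the case surfaces another way. Less testing or less response lowers the count, and a lower threshold for stopping raises it. A finding of no more DILI in primary care could then mean equal safety, fewer tests or fewer responses, and the listed outcome could not tell these apart.

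There is also a link to the primary outcome. A patient who stops before taking 90% of doses is not a completer. A team that stops less often for the same liver findings could therefore score better on completion and on this safety measure together, which weakens the safety measure as a check on a completion benefit.

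**Working it through.** **Step 1: the wording.** The outcome sentence can be read in two ways.

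- The closing condition applies to all adverse events. DILI that leads to neither stopping nor hospitalisation is then not counted.
- The condition applies only to DILI, as a named subset of a wider adverse-event count. DILI without either consequence may then enter the total as an adverse event, if it is detected, but not as DILI.

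On both readings DILI is named only with the condition attached, so on both the outcome is narrower than the incidence of DILI in the abstract and Background.

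**Step 2: how large the distortion could be.** The article gives no DILI rate, testing rate or response rate, so there is no figure of its own to reproduce. Every rate below is an assumption.

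- n = 221 per arm (Sample size section, patients providing the primary outcome).
- r = true DILI rate, the same in both arms, assumed 4%.
- q = share of DILI cases that are tested and acted on by stopping. Arm A: 0.95 × 0.95 = 0.9025. Arm B: 0.70 × 0.80 = 0.56.
- h = share of the remaining cases that are still counted, through hospitalisation, symptoms or the patient stopping. Assumed 0, 0.2, 0.5 and 1, the same in both arms.

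Expected counted events = n × r × [q + (1 − q) × h]. True cases per arm: 221 × 0.04 = 8.84.

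| h | Arm A: q + (1 − q)h | Arm B: q + (1 − q)h | Events A v B | Ratio B/A |
|---|---|---|---|---|
| 0 | 0.9025 | 0.56 | 8.0 v 5.0 | 0.62 |
| 0.2 | 0.9025 + 0.0975 × 0.2 = 0.922 | 0.56 + 0.44 × 0.2 = 0.648 | 8.2 v 5.7 | 0.70 |
| 0.5 | 0.9025 + 0.0975 × 0.5 = 0.951 | 0.56 + 0.44 × 0.5 = 0.780 | 8.4 v 6.9 | 0.82 |
| 1 | 1 | 1 | 8.8 v 8.8 | 1.00 |

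The ratio does not depend on n or r. The counts do: at h = 0 they run from 4.0 v 2.5 when r = 2% to 12.0 v 7.4 when r = 6%. If q is the same in both arms, the ratio is 1 at every h.

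**Step 3: would a liver-test definition cure it?** Count DILI from the test result, whatever was done about it, and keep the same testing rates:

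- Raw count: 8.84 × 0.95 = 8.4 against 8.84 × 0.70 = 6.2, ratio 0.74. Unequal testing still distorts the comparison.
- Among tested patients: 8.4 / (221 × 0.95) = 8.4 / 210 = 4.0%, against 6.2 / (221 × 0.70) = 6.2 / 155 = 4.0%, ratio 1.0, provided tested and untested patients have the same DILI rate.

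The denominator therefore has to be tested patients, and the tested proportion has to be shown next to the result.

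**The case against.** The case against has real weight.

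- **An acted-on liver test is not a precondition for counting.** Hospitalisation counts without any decision by the trial care team. Symptoms found at monthly review can lead to stopping. The Analysis section recognises stopping by patient choice as well as for adverse effects. This stands, and it is why 0.62 is the extreme of the illustration rather than its centre.
- **Follow-up is planned to be the same in both arms.** This also stands. A reader might infer that primary care will test or respond less and so look falsely safe. The article gives no evidence for that, and the bias could run either way or be nil. But a common schedule does not secure equal attendance or equal response, and the outcome as listed would not reveal a difference.
- **Wider data are probably collected.** Harms describes monitoring of adverse events at each monthly review, and Table 1 has an adverse-effects questionnaire at Days 30, 60 and 90. It would be wrong to infer that DILI without stopping goes unrecorded. The narrower point remains: the listed outcome does not name it.
- **The full protocol or analysis plan may hold the detail.** A numerical DILI criterion and reporting of test uptake may well be there, so their absence from a journal article is not criticised. What is visible in the article is the mismatch between its own passages.
- **Treatment-limiting or hospitalised events are a defensible pragmatic measure.** Agreed. That is a reason to keep them, and not a reason to leave DILI incidence unmeasured when it is the stated objective.
- **The absolute gap is small.** In the illustration it is about three events at most when r = 4%. Correct: the issue is how the result is read, not a large numerical effect.

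**Conclusion.** The point holds in a limited form. The secondary outcome is narrower than the objective in the abstract and Background, and those passages must be reconciled. Because stopping depends partly on the randomised care team, with unblinded data collection and different data systems by arm, the count mixes liver harm with monitoring and response. Under assumed rates of 95% tested and 95% acted on against 70% and 80%, with equal true DILI, the ratio of counted events is 0.62 if no missed case surfaces, 0.70 if 20% do and 0.82 if half do. It is 1.0 if all surface, or if testing and response are equal.

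These figures show a mechanism and are not a forecast. The stronger conclusion, that the trial's safety comparison will favour primary care, does not follow from the document. This is a cheap improvement to a secondary outcome and leaves the primary analysis untouched.

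**What to change.** Reconcile the Secondary outcomes wording with the abstract and Background. Keep the existing outcome and, before analysis, add:

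1. DILI by one numerical criterion, chosen by the sponsor and applied identically to the on-treatment liver test results in both arms, whether or not treatment was stopped, reported as a proportion of tested patients.
2. By arm, the proportion of treated patients with a liver test in the 2–4 week window.
3. Discontinuation for adverse events and hospitalisation as separate components.

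The cost is outcome wording plus extraction of results from a test already scheduled in both arms, with no new visits. The small downside is that DILI stays unknown in untested patients, so item 1 must always be read with item 2. No criterion for DILI and no stopping rule is proposed here.
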